### Participant Retention and Complete Follow-Up

Adherence to using the topography device was incentivized by paying participants US $10 per day for each day up to 5 days per week of use, checked at each lab visit. Compensation was provided for collecting and returning cigarette butts at US $30 per week for each week of participation. These payments, combined with payment for attending the laboratory visit (ie, US $20), totaled US $100 for all visits that were to occur during the 9 study weeks. For the postwashout baseline session, the compensation was US $75. The reimbursement schedule was reviewed with the participant at each visit (see Table S2 in Multimedia Appendix 2). In addition, weekly visit reminder cards were sent home with participants, which outlined next appointments and visit expectations (eg, collect all butts and use device for 5 days).

### Data Management

Study data were collected and managed using REDCap (Research Electronic Data Capture) tools that are hosted through Institution A. REDCap is a secure, web-based application that is designed to support data capture for research studies. All of the data collected were anonymized and password protected. Data were entered by trained study staff shortly after collection. All REDCap data are stored securely on a server at Institution A.

### Confidentiality

Confidentiality of data was assured by assigning code numbers to each participant survey. Participants’ identities are not linked to their responses. Any documentation of participant identities is kept in a locked filing cabinet located at the Institution A study office. Data are only accessible to personnel involved with this research, with access to servers limited by the research facility being locked at all times. All study information is maintained on secured computers and a password-protected laptop. The files on the laptop will be password protected for added security. The Institution A campus data network is protected by a perimeter firewall, and the network within the campus network is further protected by another institutional firewall.

### Statistical Methods

#### Primary and Secondary Outcomes

Descriptive statistics will be used to analyze baseline data to assess any imbalances between groups in baseline demographics and prerandomization characteristics. Stratified analyses and analyses of covariance will be performed to control for any baseline imbalances. To account for the crossover design and repeated measures, linear mixed-effects models with fixed effects for period and exposure sequence (ie, filtered then unfiltered or unfiltered then filtered) and with random effects for sex and participant will be used to analyze continuous outcomes and changes from baseline. Log transformation of nonnormal continuous measures will be performed when necessary. If data do not fit a linear model, generalized models will be considered. Model variance will be fit using a compound symmetry correlation structure with default degrees of freedom, which assumes constant variance between periods, with alternative covariance structures explored in the event of nonconvergence. For analysis of ordinal questionnaire data, we will assess for exposure and period effects using ordinal repeated-measures models with fixed effects for exposure sequence and period and with random effects for sex and participant. Prespecified cutoffs and thresholds for biomarkers and topography variables will be chosen based on a comprehensive literature review prior to conducting any analysis. Normalization and sensitivity analysis will be performed, if required. Changes in means for each continuous measure between participants and between weeks within treatment conditions will be calculated. Mean differences between exposure arms for these continuous measures will also be compared. *P* values and 95% confidence intervals will be reported when providing results from fitted models. All analyses will be performed using SAS 9.4 (SAS Institute) [41]. Noncomplier and dropout data will be utilized in mixed methods models up to the point of dropout and noncompliance for an intent-to-treat analysis. A completer-only (ie, per-protocol) analysis will also be run as a secondary analysis.

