### Intervention Description

The first week involved baseline measurements of smoking behavior and urinary biologic markers. The next 2 weeks (Weeks 2 and 3) involved filtered- or unfiltered-cigarette smoking treatments, followed by a 3-week washout period (Weeks 4-6). Week 7 involved a postwashout, repeat baseline period. The crossover condition was implemented in Weeks 8 and 9. Study cigarettes were provided during the two treatment periods (ie, 4 weeks total). ST was measured on 5 days of smoking over 8-hour periods per day during the two baseline weeks (ie, enrollment and postwashout) and during the 4 weeks of switching trials; expired CO, weight, and survey measures were assessed at all visits.

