### Study Cigarettes

Two brands of cigarettes are currently available as filtered and unfiltered: Camel and Pall Mall. Participants were provided supplies of one of these two brands throughout the study period based on their preference. After baseline measurements at the beginning of Week 2, we randomly assigned participants to smoke 2 weeks’ worth of filtered or 2 weeks’ worth of unfiltered study cigarettes. We supplied study cigarettes according to the average cigarettes smoked per day for the previous week plus 10%. For example, a participant who reported smoking 10 CPD in the previous week would be provided with a supply of cigarettes that would allow 11 CPD for the entire 2-week trial. Although it is possible that changes in CPD might result from increased supplies, participants were encouraged to smoke as normally as possible and to return any unused study cigarettes in order for us to measure changes in CPD resulting from switching.

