### Plans for Assessment and Collection of Outcomes

There were eight scheduled lab visits, each with an incentive for attendance (see Participant Retention and Complete Follow-Up section). As shown in Table S1 in Multimedia Appendix 2, these visits were to occur weekly at baseline (Week 1), during the first 2 weeks of cigarette use (Weeks 2 and 3), during the postwashout baseline (Week 7), and during the second 2 weeks of cigarette use (Weeks 8 and 9). During each visit, participants were tested for expired CO, had blood pressure and weight measurements performed, and completed surveys (see Table S1 in Multimedia Appendix 2). At Weeks 1, 3, 7, and 9, participants provided a urine sample to measure normalized cotinine and carcinogen biomarkers. All collected urine samples were stored in a –80 °C freezer. Specimens were transported from Institution B to Institution A for laboratory testing.

During visits 2-4 and 6-8, participants visited the Institution B smoking laboratory facility with their topography device, cigarette butts, and unused cigarettes (left only on Weeks 3, 4, 7, and 8). Data from the topography device were downloaded so that the number of cigarettes logged in as smoked on the CReSS device could be compared to the total number of cigarettes or butts returned, as well as the number self-reported cigarettes smoked per day. Those deemed compliant with study procedures were paid for their time and supplied with another weeks’ supply of condition-assigned cigarettes. During visit 8, the same procedure was to be followed, except that it would be the final visit and no additional study cigarettes would be provided. Due to the COVID-19 pandemic, some of these procedures were curtailed and moved to remote follow-up.

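### Baseline adjustment is tied to imbalance between groups, the wrong trigger in a crossover; the two collected baselines should always enter the exposure model as covariates, for precision

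*Protocol article*

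**What the plan says.** All the analysis rules at issue are in Statistical Methods, Primary and Secondary Outcomes.

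- Descriptive statistics are used to "assess any imbalances between groups in baseline demographics and prerandomization characteristics". The next sentence gives the response to what is found: "Stratified analyses and analyses of covariance will be performed to control for any baseline imbalances".
- The main analysis uses "linear mixed-effects models with fixed effects for period and exposure sequence", plus random effects for sex and participant. No baseline covariate is listed.
- These models "will be used to analyze continuous outcomes and changes from baseline". The two responses stand side by side. The text does not rank them or say which week is the baseline for the second period.
- On covariance: "Model variance will be fit using a compound symmetry correlation structure with default degrees of freedom, which assumes constant variance between periods".

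The design provides two baselines. Intervention Description states: "Week 7 involved a postwashout, repeat baseline period". Topography is recorded in both baseline weeks and expired CO at every visit. For urine, Plans for Assessment and Collection of Outcomes states: "At Weeks 1, 3, 7, and 9, participants provided a urine sample to measure normalized cotinine and carcinogen biomarkers". That gives one baseline and one end-of-period urine value per period.

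**The concern.** The adjustment rule is the one used for parallel groups. There, a chance imbalance between arms moves the treatment estimate. In a two-period crossover the exposure effect comes from differences within participants, so any stable difference between the two sequence groups drops out. Adjusting or stratifying because the groups differ does not repair the exposure contrast, and it lets the final model depend on what the baseline data show.

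The trigger also misses the useful information. It refers to characteristics before randomization, whereas precision can be gained from the within-person difference between the Week 1 and Week 7 baselines, and Week 7 comes after randomization. Changes from baseline, the plan's other use of baseline data, can lose precision rather than gain it. With 37 enrolled of 40 planned, precision is what is at stake. No bias in the exposure contrast is alleged.

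**Working it through.** **The plan's own figure.** Sample Size states 80% power at 20 per sequence for a 10% change in cigarettes per day. It cannot be reproduced, because no standard deviation, mean or significance level is given. The check below therefore compares variances, which need none of these.

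**Set-up.** B1 and B2 are the baselines at Weeks 1 and 7; Y1 and Y2 are the on-treatment values of the two periods. All have variance σ². The exposure contrast is taken to be the within-person difference between periods, signed by sequence. Let rw be the correlation between baseline and outcome in the same period, and rb every correlation across periods. Variances are per participant.

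**Formulas.**

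- Outcome: Var(Y1 − Y2) = 2σ²(1 − rb).
- Change from each period's own baseline: Var[(Y1 − B1) − (Y2 − B2)] = 4σ²(1 − rw), because the two changes are uncorrelated.
- Adjusted: the slope of Y1 − Y2 on B1 − B2 is b = (rw − rb)/(1 − rb), and the variance is 2σ²(1 − rb)(1 − b²).

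Relative to the outcome analysis, change is therefore 2(1 − b) and adjusted is 1 − b².

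**Compound symmetry over all four values** (rw = rb = r). Here b = 0. Change has variance 4σ²(1 − r) against 2σ²(1 − r), a ratio of 2.0 at every r. The adjusted ratio is 1.0. A simulation of 10,000 trials with N = 40 and r = 0.5 gave 2.04 for change and 1.03 for adjusted; the extra 0.03 is the cost of estimating the slope.

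**Within-period correlation at or above between-period** (rb = 0.5, in units of σ²):

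| rw | b | Outcome | Change | Adjusted |
|---|---|---|---|---|
| 0.5 | 0.0 | 1.00 | 2.00 | 1.00 |
| 0.6 | 0.2 | 1.00 | 1.60 | 0.96 |
| 0.7 | 0.4 | 1.00 | 1.20 | 0.84 |
| 0.75 | 0.5 | 1.00 | 1.00 | 0.75 |
| 0.8 | 0.6 | 1.00 | 0.80 | 0.64 |
| 0.9 | 0.8 | 1.00 | 0.40 | 0.36 |

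**Other readings of the change score.**

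- Week 1 subtracted in both periods: (Y1 − B1) − (Y2 − B1) = Y1 − Y2, ratio 1.0.
- Two treatment weeks averaged against one baseline week per period, under compound symmetry: outcome (1 − r)σ² × 4 × 0.25 = (1 − r)σ²; change (1 − r)σ² × (1 + 1 + 1) = 3(1 − r)σ²; ratio 3.0.

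**Why adjustment is not beaten.** 1 − b² is at most 1, so it is no worse than the outcome analysis. Also 1 − b² = (1 − b)(1 + b), which is at most 2(1 − b) because b ≤ 1, so it is no worse than the change analysis. The exception is the degrees of freedom spent on the slopes.

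**The case against.** A reader might infer that the plan doubles the variance of its exposure contrast. The text does not support that. The outcomes themselves are also analysed, so any inflation affects only the change analyses. The baseline to be subtracted is not named, and with a common Week 1 baseline nothing is lost. Compound symmetry is stated for the fitted model; carrying it over to the baseline weeks is an added assumption. Measurements within a period lie closer together than measurements across the 3-week washout, so rw above rb is plausible and change scores could even win. All of this stands.

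A reader might also infer a large fall from the stated 80% power. That would mean treating the 80% as exact for the outcome analysis, for which the inputs are missing. The other stated inputs (f = 0.35, r = 0.50 as the lower bound, N = 40, with two-sided 5% assumed) give 99% for two within-subject measures, so Sample Size offers no single starting point. No power loss is claimed.

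A third inference is that the cigarette supply confounds the comparison, since Study Cigarettes concedes that "it is possible that changes in CPD might result from increased supplies". Supply follows the same rule in both treatment periods, so a common shift cancels in the exposure contrast. It can affect only changes within a condition.

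Finally, an analysis plan not shown may settle which response is primary and which baseline is used, and Sample Size gives a reason for interest in sex. Both are fair: the silence is not the finding, and sex-specific summaries are legitimate. The stated imbalance rule remains a poor one for this design.

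**Conclusion.** The point holds as a matter of precision and prespecification. Imbalance between groups is the wrong trigger, and routine adjustment for the baselines already collected is at least as precise as raw values or change scores at every correlation checked. The gain over raw values runs from nothing (rw = rb) to a variance of 0.36 against 1.00 (rw = 0.9, rb = 0.5). The gain over own-period changes is a factor of 2 under compound symmetry across all four values, and shrinks as rw rises.

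The sizes rest on equal variances, equal between-period correlations and one value per period. Which row of the table applies is unknown, but the preference for adjustment does not depend on it. Using Week 7 as a covariate relies on the plan's own assumption that the washout is sufficient.

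**What to change.** For outcomes measured at Weeks 1 and 7:

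1. Make the on-treatment value the response for the exposure contrast.
2. Always include two covariates: the period-specific baseline and the participant's mean of the two baselines. The second keeps between-person and within-person slopes apart, so that the within-person baseline difference does the work.
3. Drop the imbalance-triggered covariance and stratified analyses as the route to the exposure estimate. Sex-specific summaries may stay as exploratory.
4. Report changes from baseline within each condition as descriptive only.

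The cost is a change of wording and one or two degrees of freedom; no new data are needed. The article says that analysis is under way, so the change should be dated and recorded before exposure estimates are seen, or reported as made afterwards.

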### Study Objectives

This is a pilot study that will inform a possible larger clinical trial. The research question for the overall project is as follows: *What is the impact of switching smokers of filtered cigarettes to unfiltered cigarettes on smoking behavior and toxic exposures?* The specific aims are as follows:

Determine smokers’ satisfaction and attitudes toward smoking cigarettes if they were to switch from smoking filtered to unfiltered cigarettes.Measure changes in smoking topography (ST) (ie, puff count and puff volume) and cigarettes smoked per day, via butt counts and self-report, among smokers who change to unfiltered cigarettes for 2 weeks compared with these measures while smoking filtered cigarettes.Measure changes in urinary cotinine, 4-(methylnitrosamino)-1-(3-pyridyl)-1-butanol (NNAL), and volatile organic compound (VOC) excretion among smokers who smoke unfiltered cigarettes for 2 weeks compared to smoking filtered cigarettes.

Study results may inform proposed state or local legislation to ban the sale of single-use filtered cigarettes in order to eliminate the environmental impact of improperly discarded, poorly degradable plastic cigarette filters as toxic waste.

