### Overview and Trial Design

While the risks of smoking any type of tobacco product are now clear to the public, there has never been a clinical trial comparing changes in biochemically measured exposures, perceptions, topography, and other behavioral elements of cigarette smoking when switching from filtered to unfiltered cigarettes (ie, there have been no studies reported in PubMed or ClinicalTrials.gov as of October 2020). If large-scale trials were needed to definitively answer concerns that policy makers, smokers, and the general public have regarding any potential adverse effects of eliminating filtered cigarettes from the market, it would be important to ascertain the practicality and validity of measures used for such trials. General perceptions of filtered cigarettes and their safety, palatability, and composition have been measured through national panel surveys (publication in progress), but actual changes among smokers switching between filtered and unfiltered cigarettes can only be measured in a clinical trial. Further, to eliminate exposure bias, a trial in which the order of exposure is randomized is most appropriate.

We have completed an open-label, randomized, 9-week, two-sequence, two–treatment condition, crossover clinical trial of 37 adult filtered-cigarette smokers who switch to unfiltered cigarettes. We will evaluate this pilot study’s approach as to its applicability for a follow-up research project with a larger sample size.

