### Sample Size

The study sample size is 40 participants, sufficient to detect moderate within-subject effect sizes (*f*=0.35) with a moderate correlation between repeated measures (*r*>0.50). This two-by-two crossover design has statistical power of 80% for a sample size of 20 in each group to detect an effect size of 10% change in average number of cigarettes smoked per day. We tried to recruit at least 10 participants of non-White ethnicities. If participants prematurely discontinued from the trial prior to crossover, we attempted to recruit replacements from the eligible pool or advertise for new participants. We recruited 20 women out of the 40 participants and randomized by sex. Sex stratification is of interest because men and women may metabolize smoke differently due to differences in body size and differences in cigarette preference and behavior. Any woman who becomes pregnant during the trial will be excluded from further participation [38].

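### The crossover models list period and sequence as fixed effects but no exposure term, so as written they do not estimate the filtered–unfiltered contrast

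*Protocol article*

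**What the plan says.** Overview and Trial Design describes an "open-label, randomized, 9-week, two-sequence, two–treatment condition, crossover clinical trial of 37 adult filtered-cigarette smokers". Study Objectives puts the question as "What is the impact of switching smokers of filtered cigarettes to unfiltered cigarettes on smoking behavior and toxic exposures", and Sample Size justifies the numbers by a within-person effect: "The study sample size is 40 participants, sufficient to detect moderate within-subject effect sizes".

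Statistical Methods (Primary and Secondary Outcomes) then sets out the analysis:

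- Continuous outcomes: "linear mixed-effects models with fixed effects for period and exposure sequence (ie, filtered then unfiltered or unfiltered then filtered"), together "with random effects for sex and participant will be used to analyze continuous outcomes and changes from baseline".
- Ordinal questionnaire data: "we will assess for exposure and period effects using ordinal repeated-measures models with fixed effects for exposure sequence and period", again with sex and participant random.
- A further sentence: "Mean differences between exposure arms for these continuous measures will also be compared". It names no model, test or adjustment.
- Reporting: P "values and 95% confidence intervals will be reported when providing results from fitted models".

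Neither model is given a fixed effect for the cigarette being smoked or a period-by-sequence interaction, and no other section supplies one.

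**The concern.** The parenthesis in the linear-model sentence defines exposure sequence as the order of the two conditions. That factor is constant for each participant and cannot stand for the product smoked in a given period. The models therefore hold a term for time and a term for randomized group, but none for the intervention.

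The ordinal sentence is also at odds with itself: it promises exposure effects, and the terms it lists cannot give them.

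The inferential results are to come from the fitted models. If these were coded literally, no reported coefficient, P value or interval would answer the research question for any crossover outcome. The term with exposure in its name would be sequence, which reflects carryover or a group difference.

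**Working it through.** **The plan's own figure.** The only related number is the 80% power for a 10% change in cigarettes per day with 20 per sequence. It cannot be reproduced, because no SD is given. With N = 40 and a two-sided 5% test (assumed), 80% power needs a standardized within-person difference of 0.4546, that is, an SD of the difference of 10% / 0.4546 ≈ 22% of mean consumption. The point here does not depend on that figure.

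**Cell means.** Let the baseline level be a, the period effect π, the sequence effect σ and the effect of unfiltered versus filtered δ.

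| Sequence | Period 1 | Period 2 |
|---|---|---|
| Filtered then unfiltered | a | a + π + δ |
| Unfiltered then filtered | a + σ + δ | a + σ + π |

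**What each listed term estimates, with equal sequences.**

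- Period is the average within-sequence change: [(π + δ) + (π − δ)] / 2 = π.
- Sequence is the difference of the sequence averages: (2a + 2σ + π + δ)/2 − (2a + π + δ)/2 = σ.

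δ cancels from both.

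**What the research question needs.** The exposure contrast is half the difference between the within-sequence changes: [(π + δ) − (π − δ)] / 2 = δ. This is the period-by-sequence interaction. A model with only additive period and sequence terms gives both sequences the same fitted change, so its fitted value for the contrast is (π − π)/2 = 0 whatever the data show.

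**Rank check.** Over the four cells, intercept, period and sequence have rank 3. Adding an exposure column gives rank 4, as does adding period × sequence. The projection of centred exposure on the three listed columns is zero to rounding error.

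**Simulation.** 2,000 trials per effect size, 20 per sequence, no true period or sequence effect, within- and between-participant SD 1. The effect sizes are illustrative and are not taken from the trial.

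| True δ | Mean period estimate | Mean sequence estimate | Mean exposure contrast | Period test rejects at 5% when exposure is omitted |
|---|---|---|---|---|
| 0 | 0.00 | 0.01 | −0.01 | 5.2% |
| 1 | −0.006 | 0.009 | 1.008 | 1.3% |
| 5 | −0.006 | 0.005 | 4.998 | 0.0% |

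The last column uses a one-sample t test on the within-person differences as a stand-in for the model's period test. It shows where the omitted effect goes: into the error term, which makes the period test conservative. In one mixed-model fit with δ = 5 the residual variance was 8.13 without the exposure term (with optimizer warnings) and 0.85 with it.

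**Variations.**

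- Change from each period's baseline, which the plan also mentions, uses the same four cells and terms, so the result is unchanged.
- Coding individual weeks as periods adds columns for time, but additive time and sequence terms still do not contain the interaction.
- The article reports 37 participants and no split by sequence. If the split were 19/18 (assumed) with complete data, the period estimate would become π + (19δ − 18δ)/37 = π + δ/37. It would pick up about 3% of the exposure effect, which is no usable estimate of it.

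**The case against.** The best defence is that intent is plain. The ordinal sentence aims at exposure effects, the exposure arms are to be compared, P values and intervals are mentioned immediately afterwards, and the aims and crossover rationale describe a within-person comparison. On this view the article has only shortened a list of terms, and an analyst would put exposure in. That is probably what happened, and it stands as an account of the cause.

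It does not repair the text. The section does not leave the model to another document: it gives fixed effects, random effects, covariance structure, degrees of freedom and software. An analysis plan that named exposure would conflict with this published list. The analyses of covariance mentioned earlier in the section are there to handle baseline imbalance and name no exposure term either.

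It is also fair to say that the simulation measures no harm in this trial. The zeros follow from the design, and the consequences arise only if the list is coded literally.

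Two stronger readings are tempting and unsupported. A reader might infer that the exposure-arm comparison is unpaired, unadjusted for period and made outside the models. The sentence names no method, so none of this can be read from it. A reader might then conclude that the comparison should be dropped. It is instead the clearest evidence that the contrast is intended, and it may well mean model-based differences.

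**Conclusion.** The point holds for the models as written. Both the linear and the ordinal specification omit the one term that carries the trial's question, and the ordinal sentence contradicts its own aim. The size is categorical: fitted literally, the models give no estimate of the exposure effect for any crossover outcome.

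This rests on the two-by-two structure and on the article's own definition of sequence, not on any assumed variance or effect size. Exact cancellation from the period term also needs equal sequences, but modest imbalance changes nothing of substance.

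A reader might infer that the trial cannot answer its question. The documents do not support that: the design and data allow the contrast to be estimated, and the intention to compare exposures is stated. It is a probable wording omission that should be corrected before model results are reported.

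**What to change.** In both the linear and the ordinal model sentences, list exposure (unfiltered versus filtered) as a fixed effect alongside period and sequence. Name the exposure coefficient with its 95% CI as the result for each crossover outcome. Keep the sentence on mean differences between exposure arms, and state that these are the within-participant, period-adjusted estimates from that model. The treatment of sex is a separate matter and need not change here.

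The cost is a few words in each of these sentences and one term per model. No new data or change in sample size is needed. The article says that analysis is underway, so any model already fitted from the literal list would have to be refitted.

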### Assignment of Interventions: Allocation

Once a participant was deemed eligible for the trial remotely by Institution A, trial personnel at Institution B followed up with the participant to schedule the initial trial appointment (ie, the enrollment, or baseline, visit). Participants who did not meet the eligibility criteria were not included in the trial. Recruitment and enrollment was a continuous process (ie, up to 10 participants at a time), which enabled us to utilize topography devices and lab facilities most efficiently. Randomization, stratified by sex, was based on a table of random numbers, and records were placed in sealed envelopes. A total of 20 participants were assigned to be first switchers following their enrollment (ie, baseline) visit at Institution B. These participants were then tested on individualized schedules (ie, not as a group), with each participant committing to 9 weeks of trial time, including a washout period at midtrial. All subjects had first smoked filtered Camel or Pall Mall cigarettes for at least two weeks prior to beginning the trial, according to the inclusion criteria. This standardized their exposure to a brand that was used as an unfiltered variety in the trial.

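### Sex, a two-level stratification factor, is fitted as a random effect, so whether it is adjusted for depends on the data and intervals for condition means can be inflated; a fixed effect is a minor, nearly free correction

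*Protocol article*

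**What the plan says.** In the protocol article, Statistical Methods (Primary and Secondary Outcomes), continuous outcomes are to be analysed by "linear mixed-effects models with fixed effects for period and exposure sequence", and the random part is given in the words "with random effects for sex and participant". Questionnaire items get the same treatment: "ordinal repeated-measures models with fixed effects for exposure sequence and period and with random effects for sex and participant". On covariance the section adds "Model variance will be fit using a compound symmetry correlation structure with default degrees of freedom", with other structures to be tried only if the model fails to converge.

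Sex enters the design in two other places. The allocation section states "Randomization, stratified by sex, was based on a table of random numbers". The Sample Size section states "We recruited 20 women out of the 40 participants and randomized by sex" and gives the reason: "Sex stratification is of interest because men and women may metabolize smoke differently".

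Sex is therefore a known two-level design factor. The random specification appears twice, so it reads as a deliberate choice and not a slip of the pen.

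**The concern.** A random effect treats the observed levels as draws from a larger population and estimates the variance of that population. Two sexes give one degree of freedom for it. Two things follow.

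- **Estimate at zero.** Sex then leaves the model. Adjustment for the factor used in randomization is decided by the data and not by the plan, and it can differ from one outcome to the next.
- **Estimate above zero.** Half the sex variance is added to the variance of every model-based mean. The plan promises 95% confidence intervals from fitted models, so reported means under filtered and unfiltered smoking would carry uncertainty about which sexes were sampled. That uncertainty has no meaning here, since both sexes are in the trial by design.

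At stake are the reported condition means, the sequence term, participants who contribute one period only, and the stability of the ordinal fits. The main within-person comparison is not at stake.

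**Working it through.** The plan gives no figure of its own for the sex term, so there is none to reproduce. The stated 80% power does not bear on this point.

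**Inputs.** Two sexes. Planned 20 women of 40 (Sample Size), hence 20 v 20. Enrolled 37 (Results); the split by sex is not given, and 18 v 19 is assumed. Differences are in units of the SD of participant means within sex (1 below). The fixed part between participants has an intercept and sequence; sex takes one more degree of freedom, so the residual df is n − 3.

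**Step 1: how often the sex variance is zero.** In balanced data the REML sex variance is zero when the F ratio for sex among participant means is at most 1. So P(zero) = P(F(1, n − 3; λ) ≤ 1), with λ = d² × n₁n₂/(n₁ + n₂). At 18 v 19, n₁n₂/n = 342/37 = 9.243 and the residual df is 34.

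| True difference d | λ | P(zero), 18 v 19 | P(zero), 20 v 20 |
|---|---|---|---|
| 0 | 0 | 0.676 | 0.676 |
| 0.25 | 0.578 | 0.550 | 0.542 |
| 0.5 | 2.311 | 0.294 | 0.274 |
| 0.8 | 5.916 | 0.076 | 0.063 |

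**Step 2: check by simulation.** REML fits to 200 simulated trials per scenario (40 participants, two periods, intraclass correlation 0.5 assumed) gave zero estimates in 66%, 47.5%, 17% and 3.5% at differences of 0, 0.3, 0.5 and 0.8 total SD. On that scale the SD of participant means is √0.75 = 0.866, so these differences are 0, 0.35, 0.58 and 0.92 in the units of the table. The formula then gives 68%, 44%, 20% and 3%, which agrees within simulation error.

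**Step 3: what a non-zero estimate does to means (20 v 20).** The mean square for sex is 20 × d²/2 = 10d². The variance estimate is (10d² − 1)/20. The variance of the overall mean is that estimate divided by 2, plus 1/40. With sex fixed it is 1/40 = 0.025.

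- Observed d = 0.5: sex variance (2.5 − 1)/20 = 0.075; variance of the mean 0.0375 + 0.025 = 0.0625; standard error ratio √(0.0625/0.025) = 1.58.
- Observed d = 0.8: sex variance (6.4 − 1)/20 = 0.27; variance of the mean 0.135 + 0.025 = 0.16; ratio √(0.16/0.025) = 2.53.

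These ratios are for the mean over both conditions. The mean under one condition has a larger participant-level variance, so its ratio is a little lower. With intraclass correlation 0.5 that variance is 4/3 in the same units, and (4/3)/40 = 0.0333. The ratios are √((0.0375 + 0.0333)/0.0333) = 1.46 and √((0.135 + 0.0333)/0.0333) = 2.25. They rise towards 1.58 and 2.53 as the correlation rises.

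**Step 4: the exposure contrast.** In the same simulations, with exposure among the fixed effects, removing the random sex term left the exposure estimate unchanged and its standard error unchanged to within 0.00001. Each participant contributes both conditions, so sex cancels.

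**The case against.** The strongest reply is that the trial is about filtered versus unfiltered smoking within a person, and Step 4 shows that this comparison does not move. That stands, and it sets the weight of the point. A reader might infer that the primary comparison is invalid; the calculations do not support that.

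The reply continues that a zero estimate needs F ≤ 1, so sex drops out only when the data show little sex difference. The 68% figure belongs to the case with no true difference, where losing the term costs nothing, and at 0.8 SD the chance is only about 8%. This is fair and limits the harm. It does not justify letting the data decide whether a design factor is in the model, and it leaves the inflated intervals untouched, since these arise when sex does differ. Software also usually reports a boundary estimate, so the loss need not go unnoticed.

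A reader might also infer that the trial poses a sex question that these models cannot answer. The research question and three aims under Study Objectives do not mention sex. The Sample Size sentence gives a reason for stratifying and promises no sex contrast. An exposure-by-sex estimate needs an added interaction term whether sex is fixed or random, so its absence does not follow from the random effect.

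It is also tempting to put a chi-square interval with one degree of freedom around the estimated sex SD. That interval belongs to the mean square, not to the REML variance, from which participant noise has been subtracted. Its simulated coverage was 16% to 79% for true sex SDs from 0.1 to 1.0, so it should not be used.

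Finally, the plan allows other covariance structures and adjustment for baseline imbalance. The first applies only after nonconvergence, and a zero variance is not nonconvergence. The second does not say that sex becomes a fixed term.

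**Conclusion.** The point holds as a minor correction to a stated model. A two-level stratification factor is placed in the random part of the linear and ordinal models. As a result it goes unadjusted in roughly 8% to 68% of trials over true differences of 0.8 SD down to none. When it is retained, an observed sex difference of 0.5 to 0.8 SD inflates the standard error of the overall mean about 1.6 to 2.5 times, and slightly less for a single condition.

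The figures assume near-balanced complete data, REML with variances bounded at zero, an 18 v 19 split for the zero-variance percentages and 20 v 20 for the standard errors. The effects on one-period participants and on ordinal convergence are plausible but were not quantified, and the documents do not say how many participants have one period only. The complete-pair exposure contrast is sound in this respect.

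**What to change.** In both model descriptions under Primary and Secondary Outcomes, move sex to the fixed effects and leave participant as the random effect. This costs one between-participant degree of freedom out of about 37 participants, needs no new data, and can be done while analysis is under way. Because the trial is a pilot for a larger one, it also keeps the specification from being carried forward.

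An exposure-by-sex term is a separate, optional addition. If included, label it exploratory and report it with its confidence interval. At 20 v 20, power is only about 30% for an interaction as large as the exposure effect detectable with 80% power (0.455 SD of the within-person difference, two-sided 5% level assumed).
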